## Abstract

**Background:**

Clinical Practice Guidelines recommend using peripheral blood pulse measuring as a screening test for Atrial Fibrillation. However, there is no adequate evidence supporting the efficacy of such procedure in primary care clinical practice. This paper describes a study protocol designed to verify whether early opportunistic screening for Atrial Fibrillation by measuring blood pulse is more effective than regular practice in subjects aged 65 years attending primary care centers.

**Methods/design:**

An cluster-randomized controlled trial conducted in Primary Care Centers of the Spanish National Health Service. A total of 269 physicians and nurses will be allocated to one of the two arms of the trial by stratified randomization with a 3:2 ratio (three practitioners will be assigned to the Control Group for every two practitioners assigned to the Experimental Group). As many as 12 870 patients aged 65 years or older and meeting eligibility criteria will be recruited (8 580 will be allocated to the Experimental Group and 4 290 to the Control Group). Randomization and allocation to trial groups will be carried out by a central computer system. The Experimental Group practitioners will conduct an opportunistic case finding for patients with Atrial Fibrillation, while the Control Group practitioners will follow the regular guidelines. The first step will be finding new Atrial Fibrillation cases. A descriptive inferential analysis will be performed (bivariate and multivariate by multilevel logistic regression analysis).

**Discussion:**

If our hypothesis is confirmed, we expect Primary Care professionals to take a more proactive approach and adopt a new protocol when a patient meeting the established screening criteria is identified. Finally, we expect this measure to be incorporated into Clinical Practice Guidelines.

**Trial registration:**

The study is registered as NCT01291953 (ClinicalTrials.gob)

## Background

Atrial fibrillation (AF) is defined as a cardiac arrhythmia involving irregular atrial activation, uncoordinated atrial systole and ineffective ventricular filling. ECG shows no P wave but displays fast fibrillation waves different in form, size and rhythm that lead to an irregular ventricular response. Echocardiogram shows no mitral A wave valvular movement [1]. AF is the most frequent arrhythmia in clinical practice and a growing challenge to public health due to population aging. The estimated prevalence of AF is 0.4-1% in the general population and increases with age up to 5-6% in the population aged > 65 years, and 8% in subjects aged 80 years or older [2,3]. Similarly, while the incidence of AF is < 0.1% per year in subjects aged < 40 years, it increases to above 1.5% per year in women and 2% in men aged > 80 years [4]. The incidence of AF was expected to increase 5-fold by the year 2010 [5-8]. According to the Framingham Heart Study, lifetime risk for AF is 1 in 4 in men and women aged 40 years or older. Lifetime risks remain greater even in absence of congestive heart failure or myocardial infarction (1 in 6) [9]. AF is one of the fastest-growing cardiovascular epidemics of the 21^st^ century, as it is one the major causes of morbidity and mortality, and it increases death risk, congestive heart failure and the risk for embolisms –including strokes [6,10-12]. One in every six strokes occur in subjects with AF [13,14], and the increased risk for ictus depends on the number of additional risk factors. In addition, the quality of life of these patients is severely impaired, mainly due to their inability to perform daily activities as a result of the risk of exacerbation of symptoms [15]. Over the last 20 years, admissions for AF have increased by 66% as a result of population aging, the increasing prevalence of chronic heart diseases, the more frequent diagnosis by ambulatory control mechanisms, and other factors [16].

A third of patients have asymptomatic AF. AF evolves from rare asymptomatic episodes to longer and more frequent strokes until it becomes permanent. Occasionally, AF is detected after an ECG performed during a hospitalization without a principal discharge diagnosis of AF [1]. The treatment of these patients represents a challenge continuously revised by experts [17]. The risk for cardioembolic processes in these patients significantly decreases with preventive treatment with oral anticoagulant drugs, which reduce relative risk by 68% and relative mortality by 2.5%, as compared with placebo [1].

Before recommending a screening test, a set of epidemiologic requirements should be met. The goal is to achieve a significant improvement in the prognosis of AF, since the decrease in the associated morbidity and mortality rates is greater when screening is performed. Early screening for AF might be highly beneficial for patients. The systematical population screening –especially in the elderly, as they are at a greater risk for AF and its complications–would be of great interest. The AF AWARE (Atrial Fibrillation Awareness And Risk Education) study, performed in 2009 in 11 countries with 810 cardiologists and 825 patients with AF concluded that early AF screening and treatment may help reduce severe AF-related risks [18]. Some studies have assessed the role of screening for AF, although it is more frequently detected and diagnosed when it becomes symptomatic [19-24]. Fitzmaurice et al [25] studied the cost-effectiveness of systematic screening versus the performance of ECG, and they concluded that blood pulse measuring is the best practice in cost-effectiveness terms; finally, they suggested the need for further studies assessing the efficacy of early screening for AF versus regular clinical practice. The practice of screening for AF in the elderly meets most of the criteria established by Wilson & Jungner to evaluate its implementation [26]: it is a usual and comprehensive process; it can be detected by simple procedures (blood pulse measuring is inexpensive, simple and harmless); diagnosis of AF can be confirmed by a simple and highly sensitive and specific test (ECC); screening for AF is free of iatrogenic effects, and the risk for complications or side effects as stroke can be significantly reduced with the available treatments. Two screening procedures have been proposed: opportunistic screening (performing screening when the practitioner sees a patient for any reason), or systematic (encouraging the patient to undergo a screening). There is evidence that the opportunistic option is the most appropriate [27].

The most recent Clinical Practice Guidelines recommend measuring blood pulse to test for suspected AF, and performing ECG to confirm a diagnosis of AF [28]. However, there is not adequate evidence supporting this recommendation, especially in the context of Primary Care.

### Research objectives

The three main aims of this study are:

To establish the percentage of patients with AF identified “de novo” by radial pulse assessment as compared to those discovered by regular clinical practice.

To know the amount of asymptomatic AF patients, and the symptoms and clinical signs showed by symptomatic AF patients.

To identify the different AF typologies following expert panels’ classifications.

Complementary objectives are:

To know the socio-demographics of the population with AF.

To identify health problems associated with this condition (comorbidity and risk factors).

To know the previous treatment followed by these patients.

## Methods/design

### Design of the study

A open, cluster, multicenter, two-arm, individual randomization, controlled trial of the efficacy of performing opportunistic screening versus regular clinical practice (Figure 1).

**Figure 1 F1:**
[figure not shown]
Design of DOFA-AP study.

### Setting

Spanish National Health system. Primary Care physicians and nurses working in health centers in Barcelona, Córdoba and Badajoz. The study will have a duration of 12 months; fieldwork will have a duration of 5 months.

### Participants

The selection criteria were:

* Eligibility Criteria:

Men and women aged ≥ 65 years attending their health center for any reason.

* Exclusion Criteria:

Previous AF diagnosis (prevalent cases): we will measure the characteristics of patients previously diagnosed with AF and process the data obtained as existing cases, for statistic purposes.

### Sample size

The primary endpoint will be the percentage of AF cases; sample size estimation was performed according to the results obtained by Fitzmaurice DA [25] in its trial of effectiveness, using EPIDAT 3.1 software [29] and within the following criteria:

Risk in exposed patients: 1.63%; risk in non-exposed: 1.012%, expected relative risk: 1.62%.

Controls –CG– per case –EG–: 0.5 (1:2 ratio). With this ratio, we intend to optimize and make the study feasible, as it will be more difficult to identify and recruit controls.

Confidence level: 95.0%; accuracy: 80%; the resulting sample size is 7 722 subjects for the EG, and 3 861 subjects for the CG. As we estimated a non-response rate of 10%, we adjusted the formula Nf= Ni [1/(1-R)]=7 722 [1/(1-0,10)]= 8 580 (GE) and del GC= Ni [1/(1-R)]=3 861 [1/(1-0,10)]= 4 290. Consequently, the total N= 8 580 + 4 290=12 870 subjects. As this is a cluster design study and according to the study referenced above [25], at least 100 health professionals should recruit at least 12 000 patients. Since the probability of finding patients meeting the eligibility criteria is much lower for the CG than for the EG, stratified randomization will be used to assign at least 200 primary care health professionals to the two groups, with a 2:3 ratio. In other words, there will be three CG health practitioners for every two EG practitioners.

Patient selection will be performed by consecutive sampling.

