### -Statistical Analysis

Statistical analysis will be performed with the statistics analysis software EPIDAT 3.1 [29], SPSS [33], and WLwiN 2.02 [34]. It will include:

a. Descriptive Analysis: characteristics of the population under study (sociodemographic variables): central tendency, dispersion and position measures for quantitative variables; and tabulation and calculation of relative frequencies for qualitative variables. A calculation of major estimators with their corresponding 95% confidence intervals (CI95%) will be performed.

b. Bivariate Analysis: We will examine basal comparability between the two groups using the chi-square test or Fisher’s test (proportion comparison test), or by Student’s t-test (mean comparison test after testing normal distribution). Then, the AF dependent variable will be examined and crossed with the sociodemographic variables and other independent or prognostic variables of interest. On such purpose, we will use Pearson’s chi square tests or Fisher’s test (qualitative variables), and Student’s t-test or ANOVA (quantitative variables). All contrasts will be bilateral (p < 0.05).

c. Analysis of the relationship between the type of intervention and the primary variable of the study (AF): contingency tables, square chi test, relative risk estimation), attributable risk and number of subjects to be treated, with their respective CI95%.

d. Multivariate Analysis: A multi-level logistic regression or multiple logistic regression will be performed to compare effects of the strategy on both groups (Odds Ratio) adjusting the model for potential prognostic and / or confounding candidate variables. When multiple logistic regression is used, these variables will be introduced by the “Enter” technique. Significance will be > 0.10 according to Wald’s test.

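### The stated 7 722 EG / 3 861 CG does not follow from the stated inputs; at that size the planned chi-square test has about 77–78% power before clustering, not 80%

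*Protocol article*

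**What the plan says.** The Sample size section prints a complete calculation.

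- Risks and effect: "Risk in exposed patients: 1.63%; risk in non-exposed: 1.012%, expected relative risk: 1.62", the last figure followed by a percent sign.
- Patient ratio: "Controls –CG– per case –EG–: 0.5 (1:2 ratio"), so two EG patients for each CG patient. The stated reason is that controls will be harder to find and recruit, so a larger EG is clearly intended.
- Error rates: "Confidence level: 95.0%; accuracy: 80"%. Here accuracy can only mean power.
- Result: 7 722 EG and 3 861 CG, inflated for 10% non-response to 8 580 and 4 290, total 12 870. The Abstract repeats the three inflated figures.

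The Statistical Analysis section says of the tests: "All contrasts will be bilateral (p < 0.05"). For the relation between intervention and AF it plans "contingency tables, square chi test, relative risk estimation". The Sample size section names the software (EPIDAT 3.1) but not the formula. It applies no intracluster correlation or design effect.

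**The concern.** Every input needed to check the result is in the text, so the check does not depend on an analysis plan or a fuller protocol. The stated pair is smaller than the inputs imply for the planned test. If so, the trial is described as having 80% power for its primary comparison when it has somewhat less, and the recruitment target of 12 870 is built on the wrong base. The inputs also disagree slightly with each other: the quoted relative risk is not the ratio of the quoted risks. A reader therefore cannot tell which values went into the software.

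**Working it through.** **Inputs.** p1 = 0.0163 (EG), p0 = 0.01012 (CG), k = CG/EG = 0.5 and power 80% (z = 0.8416), all from Sample size. Two-sided 5% (z = 1.9600) and chi-square, from Statistical Analysis.

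**Step 1: the non-response step reproduces.** 7 722/0.9 = 8 580 and 3 861/0.9 = 4 290, total 12 870. Any error is in the base figures.

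**Step 2: sample size at the stated ratio.** Pooled two-proportion formula:

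n(EG) = [1.9600·√(p̄(1−p̄)(1+1/k)) + 0.8416·√(p1(1−p1) + p0(1−p0)/k)]² / (p1−p0)², with p̄ = (p1 + k·p0)/(1+k)

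- p̄ = (0.0163 + 0.5 × 0.01012)/1.5 = 0.01424
- first term 0.40221, second term 0.15984, sum 0.56205
- n(EG) = 0.56205²/0.00618² ≈ 8 271.2, rounded up to **8 272**; n(CG) = **4 136**; total 12 408
- after non-response: 8 272/0.9 → 9 192 and 4 136/0.9 → 4 596, total 13 788

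Against the stated totals the gap is 12 408 − 11 583 = 825 evaluable patients (825/11 583 = 7.1%), or 13 788 − 12 870 = 918 recruited.

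**Step 3: variants at the stated ratio.**

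| Variant | EG | CG |
|---|---|---|
| Pooled, CG risk 1.012% | 8 272 | 4 136 |
| Pooled, CG risk 1.01% | 8 213 | 4 107 |
| Pooled, RR 1.62 taken literally (CG 1.63/1.62 = 1.006%) | 8 103 | 4 052 |
| Pooled with continuity correction | 8 750 | 4 375 |
| Pooled, one-sided | 6 478 | 3 239 |
| Arcsine | 7 926 | 3 963 |
| Unweighted mean of the two risks | 7 847 | 3 923 |
| Unpooled variance | 7 413 | 3 706 |
| **Stated** | **7 722** | **3 861** |

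None gives the stated pair.

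**Step 4: the reversed ratio.** With k = 2 and the stated 1.012%, the pooled formula gives 3 889 EG and 7 778 CG, within 0.7% of the stated numbers but on opposite arms. With CG risk 1.01%:

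- p̄ = (0.0163 + 2 × 0.0101)/3 = 0.012167
- n(EG) = (0.26316 + 0.12206)²/0.0062² ≈ 3 860.4, rounded up to 3 861; n(CG) = 2 × 3 861 = 7 722

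These are the protocol's two numbers to the unit, with the arms exchanged.

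**Step 5: power at 7 722 EG / 3 861 CG.**

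- null standard error: √(0.01424 × 0.98576 × (1/7 722 + 1/3 861)) = 0.0023353
- alternative standard error: √(0.0163 × 0.9837/7 722 + 0.01012 × 0.98988/3 861) = 0.0021613
- (0.00618 − 1.9600 × 0.0023353)/0.0021613 = 0.742, so power = **77.1%**

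Simulating the Pearson chi-square test (2 million trials) gives **77.7%**. With RR 1.62 taken literally, the formula gives 78.0% and simulation 78.6%.

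**Step 6: detectable effect.** Holding EG at 1.63%, 80% power at 7 722 / 3 861 needs a CG risk of 0.992%, so RR = 1.63/0.992 ≈ 1.64.

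**Step 7: the stated RR.** 1.63/1.012 = 1.611, which rounds to 1.61.

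**The case against.** **The formula is not named, and the answer depends on it.** This is the strongest objection, and part of it stands. The arcsine and unweighted-mean versions come within 3% of the stated N, and under the unpooled formula 7 722 / 3 861 has 81.6% power. However, none of them returns the stated pair. The planned test is a chi-square, for which the pooled form is the relevant one. Simulation of that test needs no sample-size formula and also falls below 80%.

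**The shortfall is small.** This stands. It is 1 to 3 points of power, depending on which stated input is kept. If all 8 580 / 4 290 were evaluable, power would be 81.5%, but that spends the 10% non-response allowance the section itself assumes.

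**The relative risk mismatch is close to rounding.** It is, and on its own it would not merit a comment. It matters here only because the exact match in step 4 needs yet another value of the control risk.

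Three stronger readings are tempting and are not supported:

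- *That the ratio was demonstrably entered the wrong way round.* The article does not say so. The exact match needs a CG risk of 1.01%, which the text does not give. It is a likely explanation only.
- *That exchanging the arms costs power because the low-risk arm is the more variable one.* On the risk-difference scale the higher-risk arm has the larger variance. The extra N comes from the pooled null variance, which rises when more patients are in the higher-risk arm (p̄ = 0.01424 at the stated ratio, 0.01218 reversed). With unpooled variance the direction flips: 7 413 + 3 706 = 11 119 at the stated ratio against about 4 325 + 8 650 = 12 975 reversed.
- *That the trial is seriously underpowered on this account and must recruit more.* A gap of this size does not show that. The absence of a clustering allowance is a separate matter and should not lend weight to this one.

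**Conclusion.** The point holds as an arithmetic inconsistency of modest size. From the stated inputs, the formula that matches the planned test gives about 8 272 EG / 4 136 CG, not 7 722 / 3 861. At the stated numbers, power is about 77–78% and the detectable relative risk about 1.64. This rests on a two-sided 5% chi-square test without continuity correction, the stated risks and independent patients. Clustering would lower the power further, by an amount this calculation does not address. That the stated pair does not reproduce does not depend on why; the reversed ratio remains an inference. The estimand and the analysis are unaffected.

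**What to change.** In the Sample size section:

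1. State that 7 722 EG / 3 861 CG gives about 77–78% power for the two-sided chi-square test before any allowance for clustering, with a detectable relative risk of about 1.64 at 80% power.
2. Use one consistent set of inputs: 1.63%, 1.012% and relative risk 1.61, without the percent sign.
3. Name the sample-size formula, say whether a continuity correction was used, and call the 80% figure power.
4. Check the software input for the direction of the ratio and, if it was reversed, say so.

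The cost is a few lines of wording and a slightly less favourable power figure. The recruitment target can stay at 8 580 / 4 290, so no patients are added and the Abstract's numbers need no change.

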### Randomisation

Researchers will be assigned to one of the study groups by stratified randomization based on the center and the type of health professional (GP/nurse) using EPIDAT 3.1 software [29].

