### Measurement Instruments and action program

1. A Data Collection Form (DCF) and a Procedure Manual including a Clinical Protocol based on an updated Practice Guideline will be designed [30].

2. A pilot study has already been conducted on a sample of 20 randomized patients in five health centers located in Barcelona and Córdoba, where five GP and five nurses participated. The target population was willing to undergo the test. The data collected by the DCF allowed practitioners to identify two cases of undiagnosed asymptomatic AF.

3. Communication Plan and Recruitment of Health Professionals: the project managers of the study were in charge of the dissemination of the study; in addition, a presentation of the study was performed in different health centers in Barcelona, Córdoba and Badajoz. A total of 269 health professionals at 28 health centers agreed to participate in the study (162 GPs and 107 nurses).

4. Training Plan. A presentation will be given to familiarize the participating practitioners with the study protocol. All participants will take an on-line course on how to approach patients with AF (http://www.semfyc.es/pfw_files/cma/Agenda/Sesiones_multimedia/Documentos/Diptico_referentes_fa.pdf). On the first stage, we intend to designate a practitioner as the expert in FA. The practitioner selected will take an online course to acquire the abilities and skills necessary to be able to give a training session to his/her partners.

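### The sample size treats patients as independent although practitioners are randomised, so the stated 80% power is unsupported; the size of the loss depends on an ICC that the protocol does not give

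*Protocol article*

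**What the plan says.** Practitioners are the unit allocated. The Randomisation section states: "Researchers will be assigned to one of the study groups by stratified randomization based on the center and the type of health professional (GP/nurse"). The Design of the study section adds a conflicting label, "A open, cluster, multicenter, two-arm, individual randomization, controlled trial", but the Abstract, the Sample size section and the Randomisation section all describe allocation of practitioners.

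The Sample size section prints its calculation in full:

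- Rates: "Risk in exposed patients: 1.63%; risk in non-exposed: 1.012%, expected relative risk: 1.62".
- Patient ratio: "Controls –CG– per case –EG–: 0.5 (1:2 ratio").
- Result: "Confidence level: 95.0%; accuracy: 80%; the resulting sample size is 7 722 subjects for the EG, and 3 861 subjects for the CG".
- Non-response of 10%: each arm is divided by 0.90, giving 8 580 + 4 290 = 12 870.

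Clustering is mentioned only after N is fixed: "As this is a cluster design study and according to the study referenced above [25], at least 100 health professionals". Between them, these practitioners are set a minimum of 12 000 patients. The section then raises the number of practitioners to at least 200, three control (CG) for every two experimental (EG). The reason given is that eligible control patients are harder to find. Under Measurement Instruments and action program, the number actually enlisted is larger: "A total of 269 health professionals at 28 health centers agreed to participate in the study".

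**The concern.** Patients seen by the same practitioner share that practitioner's pulse-taking and ECG reading, and the section on protection against bias itself names inadequate practitioner skill as a source of error. Outcomes within a practitioner may therefore be correlated. Any positive correlation inflates the variance of the arm comparison and lowers power below that of an independent sample of the same size. The printed calculation has no step that allows for this.

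The authors expect the result to enter clinical practice guidelines. A non-significant result would be read against a claimed 80% chance of detecting a relative risk of about 1.6. If that claim is not supported, the result could be given more weight as evidence against screening than the design warrants.

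**Working it through.** **Inputs from the protocol article.** Rates 1.63% (EG) and 1.012% (CG), difference 0.00618; 95% confidence; 80% accuracy, read as power; two-sided tests (Statistical Analysis); 7 722 and 3 861 evaluable patients; 269 practitioners enlisted, minimum 200; practitioners split 2 EG : 3 CG.

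**Assumed.** The ICC (none is given), equal cluster sizes within arm, and no extra centre-level correlation.

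**Step 1: reproduce the plan's N with no clustering.** For two independent proportions with CG half of EG, the EG number is:

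- unpooled variance with continuity correction: 7 891 (+2.2% on 7 722);
- pooled variance with an unweighted mean proportion: 7 847 (+1.6%);
- unpooled with continuity correction, CG rate taken as 1.63%/1.62 = 1.006%: 7 725.

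Two other common variants fall further away: 7 413 (unpooled, no correction) and 8 272 (patient-weighted pooled variance). The document does not name its formula, but ordinary individual-patient formulas reach its figure within 3%. Then 7 722/0.90 = 8 580 and 3 861/0.90 = 4 290 exactly. N therefore looks like an individually randomised sample size plus a non-response allowance.

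**Step 2: cluster sizes.** EG practitioners 0.4 × 269 = 107.6, so m = 7 722/107.6 = 71.8. CG practitioners 0.6 × 269 = 161.4, so m = 3 861/161.4 = 23.9.

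**Step 3: power.** Per arm, DE = 1 + (m − 1) × ICC.

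- SE1 = √[Σ p(1−p) × DE/n], using each arm's own rate.
- SE0 = √[p̄(1−p̄) × Σ DE/n], with p̄ = (7 722 × 0.0163 + 3 861 × 0.01012)/11 583 = 0.01424.
- Unpooled power = Φ(0.00618/SE1 − 1.96).
- Pooled power = Φ[(0.00618 − 1.96 × SE0)/SE1].

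Worked case, ICC 0.01:

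- DE = 1 + 70.8 × 0.01 = 1.71 (EG) and 1 + 22.9 × 0.01 = 1.23 (CG).
- Variances: 0.0163 × 0.9837 × 1.708/7 722 = 3.546 × 10⁻⁶ and 0.01012 × 0.98988 × 1.229/3 861 = 3.189 × 10⁻⁶.
- SE1 = 0.002595; SE0 = 0.002752.
- Unpooled: Φ(2.381 − 1.96) = 66%. Pooled: Φ(0.303) = 62%.

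| Assumed ICC | DE, EG / CG | Power, pooled to unpooled |
|---|---|---|
| 0 | 1.00 / 1.00 | 77-82% |
| 0.001 | 1.07 / 1.02 | 75-80% |
| 0.002 | 1.14 / 1.05 | 74-78% |
| 0.005 | 1.35 / 1.11 | 69-74% |
| 0.01 | 1.71 / 1.23 | 62-66% |
| 0.02 | 2.42 / 1.46 | 51-55% |

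With only the minimum of 200 practitioners (m about 97 and 32), power is 66-71% at ICC 0.005 and 58-62% at 0.01.

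**Step 4: detectable relative risk.** Holding the CG rate at 1.012% with 269 practitioners, the relative risk detectable with 80% power is about 1.67-1.71 at ICC 0.005 and 1.73-1.77 at 0.01 (unpooled to pooled). The planned value is 1.63/1.012 = 1.61.

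**The case against.** **The loss may be small.** The document gives no ICC, and at event rates of 1.0-1.6% even a modest ICC implies wide variation between practitioners. The coefficient of variation of true detection rates is √[ICC(1−p)/p]: 25-44% for ICC 0.001-0.002, but 78-99% for 0.01 and 110-140% for 0.02. At 0.001-0.002 power is 74-80%. If all 8 580 + 4 290 patients were evaluable, it would be 80-84% at 0.001 and 78-82% at 0.002. This stands. A reader might infer that power is well below 80% as a matter of fact; the documents do not support that without an ICC.

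**Part of the gap is the formula.** Pooled variance already gives 77% at ICC 0. At ICC 0.005 clustering itself costs about 8 points (77.1 to 68.9 pooled, 81.6 to 73.5 unpooled). This also stands, and is why the ICC 0 row must be shown.

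**The opposing ratios.** A reader might infer that placing two thirds of the patients with two fifths of the practitioners materially worsens the loss. It does not: an equal split of the 269 practitioners gains only 0.4-0.6 points at ICC 0.005 and 0.6-1.1 at 0.01.

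**Mitigation in the plan.** Enlisting 269 rather than 200 practitioners shrinks the clusters, the Statistical Analysis section names multilevel logistic regression, and confidence intervals would show imprecision. These soften the consequence but do not justify the power statement. A multilevel model pays the cost that N did not budget for. The ordinary logistic regression offered as an alternative would ignore clustering and could overstate precision.

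**Condensation.** An article may leave detail to the full protocol. Here, however, every step from the rates to 12 870 is printed, and no clustering step is among them.

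**Conclusion.** The point holds in a conditional form. The calculation is an independent-patient one, applied to a trial that its own text calls a cluster design, and the borrowed minimum of professionals and patients does not correct it. The direction is certain for any positive ICC. The size is not: the shortfall is small near an ICC of 0.001 and material from about 0.005 (69-74% with 269 practitioners). Unequal numbers of patients per practitioner would lower power further; stratification by centre could recover a little. Provided the multilevel model is used, the defect concerns power and the reading of a null result, not bias or type I error.

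**What to change.** In the Sample size section, replace the sentence on 100 professionals and 12 000 patients with:

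- the expected patients per practitioner in each arm (about 72 EG and 24 CG evaluable; 8 580/107.6 = about 80 and 4 290/161.4 = about 27 as recruited);
- an ICC range that includes 0.001-0.002, with its source;
- the variance formula used, and the ICC 0 row for reference;
- the resulting power and detectable relative risk for 269 practitioners and 12 870 patients.

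Do not claim 80% power for a relative risk of 1.61 unless a stated ICC supports it. The cost is a change of wording and a less favourable stated power. No extra patients are needed; the change discloses the power rather than restoring it.
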